## Abstract

**Background:**

Current guidelines recommend treatment of significant coronary artery disease by concomitant coronary artery bypass grafting (CABG) in patients undergoing surgical aortic valve replacement. However there is no consensus as to how best to treat coronary disease in high-risk patients requiring transcatheter aortic valve implantation (TAVI).

**Methods/Design:**

The percutaneous coronary intervention prior to transcatheter aortic valve implantation (ACTIVATION) trial is a randomized, controlled open-label trial of 310 patients randomized to treatment of significant coronary artery disease by percutaneous coronary intervention (PCI - test arm) or no PCI (control arm). Significant coronary disease is defined as ≥1 lesion of ≥70% severity in a major epicardial vessel or 50% in a vein graft or protected left main stem lesion. The trial tests the hypothesis that the strategy of performing pre-TAVI PCI is non-inferior to not treating such coronary stenoses with PCI prior to TAVI, with a composite primary outcome of 12-month mortality and rehospitalization. Secondary outcomes include efficacy end-points such as 30-day mortality, safety endpoints including bleeding, burden of symptoms, and quality of life (assessed using the Seattle Angina Questionnaire and the Kansas City Cardiomyopathy Questionnaire).

In conclusion, we hope that using a definition of coronary artery disease severity closer to that used in everyday practice by interventional cardiologists - rather than the 50% severity used in surgical guidelines - will provide robust evidence to direct guidelines regarding TAVI therapy and improve its safety and efficacy profile of this developing technique.

**Trial registration:**

ISRCTN75836930, http://www.controlled-trials.com/ISRCTN75836930 (registered 19 November 2011).

## Background

Transcatheter aortic valve implantation (TAVI) has moved into the cardiology mainstream with rapid acceptance of this new technology since the first implant in 2002 [1]. The two devices with the largest experiences are the self-expanding CoreValve Revalving™ system (Medtronic CoreValve, Luxembourg) and the balloon expandable Edwards Sapien XT valve (Edwards Lifesciences, Irvine, CA). Both are employed in patients whose peri-operative risk is deemed too high for surgical aortic valve replacement (sAVR). Coronary artery disease has a high prevalence in these patients [2–5] and shares many of the same causative factors [6]. While the matrices for these devices state that significant coronary artery disease (CAD) should preferably be treated prior to implantation, current practice is frequently not to do so. Indeed, successful PCI has been demonstrated post-implantation [7–9], as both technologies allow access to the coronary ostia. The presence of concomitant CAD has been associated with adverse procedural outcomes in sAVR [10, 11] and now also in TAVI [5]. In this higher risk cohort, with a mean age in excess of the ‘normal’ population with chronic stable angina, we must carefully evaluate any coronary artery lesion’s significance in terms of the possibly greater risks of PCI and the impact on the planned valvular intervention.

### Considerations in pre-transcatheter aortic valve implantation percutaneous coronary intervention

Among the possible advantages of revascularization prior to TAVI may be a protective effect against the ischemic burden of the procedure, including as it does periods of hypotension. The absence of contractile reserve is associated with increased mortality after sAVR [12], and significant stenoses not intervened upon could contribute to this. Surgical revascularization for multi-vessel coronary artery disease has been found to be an independent factor predictive of improvement of left ventricular ejection fraction (LVEF) after sAVR [13], and similar benefits for revascularization by PCI may exist. Improving coronary flow in symptomatic patients with significant flow-limiting stenoses may maximize this beyond the valvular intervention. Wave intensity analysis of coronary flow has demonstrated marked reduction in the diastolic suction wave in aortic stenosis (the dominant wave in coronary perfusion [14]), which significant stenosis may impair further [15].

The risks of PCI are well described: death, myocardial infarction, coronary artery bypass grafting (CABG), stroke, vascular access complications, renal insufficiency, allergy and stroke/TIA [16, 17]. PCI is also associated with an incidence of stent thrombosis of up to 1% with significant mortality [18, 19]. The presence of severe aortic stenosis could have a detrimental effect upon the ability to withstand these. Indeed, the hypotension experienced by patients during the TAVI procedure (especially during rapid right ventricular pacing) may actually increase the risk of stent thrombosis. There has been increasing recognition recently of the adverse outcomes associated with major bleeding post-PCI [20, 21]. Current opinion is to continue aspirin for life and clopidogrel for one month after bare metal stenting and 12 months after insertion of a drug-eluting stent. This would possibly impact upon bleeding complications in transfemoral, subclavian and transaortic TAVI and would certainly be of concern in patients undergoing TAVI via the transapical approach, given the direct myocardial access required. Angiography in the 24 hours, or even the 5 days, prior to sAVR has been shown to be associated with acute kidney injury post-operatively [22]. These risks may also exist if PCI and TAVI are inadequately separated or combined in a hybrid procedure. Finally, patients would require two admissions with attendant implications to cost and risk. This latter consideration might be offset against the possible reduction in length of stay in the post-TAVI period.

### Why do we need a randomized trial?

The data on coronary artery disease in TAVI and PCI in this context is certainly provocative, but there are several major limitations, given that the studies are all nonrandomized, registry-type with relatively small sample sizes.

The lack of data on pre-procedural revascularization has led to some variability between centers on the level of coronary interventions undertaken prior to implantation. A retrospective analysis by Masson *et al*. stratified TAVI patients according to myocardium at risk due to coronary artery disease, finding no difference in 30-day or 1-year mortality between the groups [4]. However the small group sizes involved would have required a mortality difference between even the two most extreme groups at 30 days of greater than one third to gain significance, limiting our use of this data. The access approach used was not included in their risk model, an important omission given the known differences in risk profiles between, for example, TF-TAVI and TA-TAVI cohorts. In the German TAVI registry, CAD was defined as previous revascularization (either PCI or CABG) OR a stenosis of ≥50% and was noted in 62% of 1,382 patients. These patients had a greater in-hospital mortality (10.0 versus 5.5%, *P* <0.01), required more frequent cardio-pulmonary resuscitation (7.8 versus 3.5%, *P* <0.01) and suffered greater 30-day mortality (log rank *P* = 0.041). But there were significant differences in the group demographics: more frequent peripheral vascular disease, lower left ventricular (LV) ejection fraction and higher logistic EuroScores in patients with CAD [23]. The Italian CoreValve registry noted that in patients with critical ostial disease, myocardial infarction (MI) within 12 months of TAVI was greater in those patients who were not revascularized prior to TAVI [24]. A recent meta-analysis of the effects of CAD upon outcome in the midterm showed no effect; but again, of seven included studies, five defined CAD as previous revascularization, and the remaining two used 50% stenosis severity [25].

The presence of pre-existing treated coronary artery disease has been identified as an adverse risk factor for procedural and long term outcome [5]. With regards to the effects of pre-TAVI PCI, Masson and colleagues performed a sub-analysis of just 15 patients in whom PCI was performed at the discretion of the individual cardiologist: the resultant selection bias in turn clouds the interpretation of any findings. The mortality in the overall group one-year after TAVI was reported as 77.9% and was found to be 80% in those with pre-emptive PCI - though no comparison between the two cohorts was performed [4]. Abdel Wahab *et al*. reported that 55 patients who underwent PCI prior to TAVI showed no difference in adverse events at either 30 days (2% versus 6%; *P* = 0.27) or 6 months (9% versus 14%; *P* = 0.42) when compared to a group undergoing isolated TAVI [26]. The feasibility of PCI for CAD in patients with severe AS has been demonstrated by Goel *et al*. in a cohort of 258 patients over a 10-year period with a favorable comparison with propensity matched patients without the aortic disease [27].

There has been a rapid, global expansion in the use of TAVI to treat aortic stenosis in patients who are not candidates for sAVR. The efficacy of this technique has been successfully demonstrated in randomized, controlled trials [28, 29] and in large registries [30, 31], and there is now a need to improve patient safety and outcome, including how to manage patients with concomitant CAD. Given the paucity of data on the issue and variation in practice and recommendations we feel a randomized controlled trial (RCT) is essential for safe evidence-based practice. ACTIVATION is the first randomized controlled trial of elective PCI prior to TAVI. Its findings will help define the optimum revascularization strategy in this procedure and help create evidence-based guidelines on this controversial issue.

## Methods/Design

### Hypothesis, design and end points

ACTIVATION is a prospective, randomized, open-label trial that aims to test the hypothesis that revascularization of significant coronary artery disease by PCI prior to TAVI (Test arm) will result in a rate of mortality and re-hospitalization at 12 months that is non-inferior to TAVI without such revascularization (control). Because the control patients in this study are receiving a CE/FDA approved valve replacement, a trial arm comparison would not be likely to demonstrate superiority in either direction.

The trial has an intentional non-inferiority design. The safety of TAVI with revascularization performed as deemed necessary by the Heart Team has been demonstrated in previous trials and registries [29, 30, 32]. From the available data detailed in the statistical design section, our hypothesis is that the no PCI strategy will have comparable effectiveness to the PCI (the active control) strategy, hopefully helping the cardiology community decide whether the extra procedure of pre-TAVI PCI can be safely avoided. From an ethical standpoint, a sham procedure in the no PCI arm could not be countenanced. Given the complexities of the TAVI procedure and the recommended Heart Team approach, we could not blind operators as to whether patients had undergone revascularization or not. To minimize bias towards the null, we have robust inclusion/exclusion criteria and clear end-point definitions and boundaries. Any deviation from the protocol in delivery of strategy will be carefully recorded, including any concomitant therapies.

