### Statistical analysis

For the primary endpoint analysis, cumulative event rate will be calculated using the Kaplan-Meier estimates, and the Greenwood standard errors for these estimates. A 95% one-sided upper confidence limit will be computed for the difference in the primary composite outcome of mortality of rehospitalization at 12 months between arms (Test - Control). The Test arm (PCI) will be judged not inferior to the Control arm (no PCI) if the upper confidence limit is less than 7.5% - the predetermined non-inferiority margin. This was chosen based upon expert opinion and precedent (PARTNER cohort A [29]). In addition to formal analysis of non-inferiority endpoints, the Kaplan-Meier curves will be presented and compared by log rank test by treatment group and hazard ratio and its 95% confidence interval will be calculated using Cox regression model. Also, the combination of the all cause mortality and time to first recurrent hospitalization will be analyzed using the unmatched win ratio approach [35].

For secondary time-to-event outcomes, event rates at 30 and 365 days will be calculated using the Kaplan-Meier method and compared by log rank test. Their hazard ratios will be estimated using Cox regression model. Outcomes with repeated measurements will be analyzed using generalized linear mixed models. Continuous variables will be summarized using number of observations, median (interquartile range) or mean (SD) depending on variable distributions, whereas categorical variables will be summarized by the number and percentage of events. Chi-square tests and Mann-Whitney methods will also be used for comparative purposes. All analyses will be performed both on intention to treat and as treated populations.

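### The design rationale treats PCI as the reference and asks whether it can be avoided, but the powered test takes no PCI as the reference and cannot answer that

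*Protocol article*

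**What the plan says.** Four places in the protocol article agree that PCI is the arm under test and no PCI the reference.

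- Abstract, Methods/Design: the hypothesis is that "the strategy of performing pre-TAVI PCI is non-inferior to not treating such coronary stenoses with PCI prior to TAVI".
- Hypothesis, design and end points, first paragraph: PCI, the arm labelled Test, "will result in a rate of mortality and re-hospitalization at 12 months that is non-inferior to TAVI without such revascularization (control" arm).
- Sample size determination: the power of at least 88.8% is for showing that TAVI after PCI is non-inferior to TAVI without it.
- Statistical analysis: a one-sided 95% upper limit is calculated on "the difference in the primary composite outcome of mortality of rehospitalization at 12 months between arms (Test - Control"), and the rule is that "The Test arm (PCI) will be judged not inferior to the Control arm (no PCI) if the upper confidence limit is less than 7.5" per cent.

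The second paragraph of Hypothesis, design and end points, which justifies the choice of a non-inferiority design, points the other way: "our hypothesis is that the no PCI strategy will have comparable effectiveness to the PCI (the active control) strategy". It gives the purpose as "hopefully helping the cardiology community decide whether the extra procedure of pre-TAVI PCI can be safely avoided". For that hypothesis it refers the reader to the data in the statistical section. That section then assumes 12-month mortality of 20% with PCI and 30% without.

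**The concern.** PCI cannot be both the test strategy and the active control. The two roles need opposite confidence bounds. An upper limit on PCI minus no PCI caps how much harm adding PCI could do. Whether PCI can be left out depends on an upper limit for no PCI minus PCI, and the article plans no margin-based test of that quantity. The log rank test, the Cox hazard ratio and the win ratio carry no margin.

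What is at stake is the sentence that the trial may write at the end. The rationale tells readers that the trial bears on omitting PCI, while the success rule limits only the excess risk of performing it. If the conflict stays, the bound that supports the conclusion could be chosen after the result is known.

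**Working it through.** **Inputs from the article.** Mortality at 12 months is 20% (PCI) and 30% (no PCI). Rehospitalization is 15% in both arms. The margin is 7.5 points, the limit is one-sided 95%, N is 310 and loss to follow-up is 5%.

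**Assumptions not in the article.** Allocation is 1:1. Death and rehospitalization are independent. A difference of two proportions stands in for the Kaplan-Meier difference.

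**Step 1: reproduce the stated power.**
- Composite with PCI: 1 - 0.80 × 0.85 = 0.320.
- Composite without PCI: 1 - 0.70 × 0.85 = 0.405.
- Evaluable per arm: 155 × 0.95 = 147.25, taken as 147.
- SE = sqrt[(0.320 × 0.680 + 0.405 × 0.595)/147] = sqrt[(0.2176 + 0.2410)/147] = 0.0559.
- Power = Phi[(0.075 + 0.085)/0.0559 - 1.645] = 88.9%, against a stated 88.8%.
- In reverse, 88.8% power needs 147 per arm, and 294/0.95 rounds up to 310.

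The sample size was therefore set for PCI non-inferior to no PCI. If the components are simply added (35% v 45%), the same test has 92.4% power, a poorer match.

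**Step 2: what a positive result looks like at this size.**
- Half-width of the one-sided limit: 1.645 × 0.0559 = 9.2 points, which is more than the margin.
- Success needs d + 9.2 < 7.5, where d is observed PCI minus no PCI. So d must be below about -1.7 points.
- The upper limit for no PCI minus PCI is -d + 9.2. At d = -1.7 it is about 10.9 points, and it rises as d falls.
- With the additive composite (SE 0.0568, half-width 9.3) the two figures become about -1.8 and 11.2 points.

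Both non-inferiority statements can hold together only if the half-width is below 7.5 points, which would need event rates under about 19%. In 400,000 simulated trials for each of four scenarios (planning rates, additive rates, equal rates of 36% and of 40.5%), no trial that met the planned rule also showed no PCI non-inferior by 7.5 points. Under the planning rates, the median upper limit for no PCI minus PCI among positive trials was 18.6 points.

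**Step 3: what the opposite bound could deliver.** If the true composite rates are equal at p, power at N = 310 is Phi[0.075/sqrt(2p(1-p)/147.25) - 1.645].

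| Common rate (assumed) | Power at 310 | Total N for 80% | Total N for 88.8% |
|---|---|---|---|
| 32% | 39.5% | 1,009 | 1,335 |
| 40.5% | 36.9% | 1,116 | 1,478 |
| 45% | 36.3% | 1,148 | 1,518 |

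The totals use n per arm = (1.645 + z)² × 2p(1-p)/0.075², with z = 0.842 for 80% power, and allow for 5% loss. At 32% and 80% power this is 479 per arm, and 958/0.95 rounds up to 1,009.

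**The case against.** The strongest reply is that the prespecified analysis is coherent. The abstract, the opening hypothesis, the power statement and the decision rule all agree, and the rule says plainly that it is PCI that will be judged not inferior. The outlier is one rationale sentence, with no margin attached, that ends in a hope. This stands. A reader might infer that the test runs against the trial's stated question, but the documents do not support that, because the test matches the formal hypothesis. The fault is confined to a rationale that contradicts it.

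A reader might also infer that the protocol intends to present a positive result as grounds for dropping PCI. It nowhere says so, and a result that visibly favours PCI is unlikely to be read that way. Nor is it a defect that the rule would be met if PCI were strongly beneficial, since that is true of any non-inferiority test.

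Finally, under the planning rates the reversed test would succeed only 3.4% of the time: Phi[(0.075 - 0.085)/0.0559 - 1.645]. It is tempting to call that a loss of power. It is correct error control, because the assumed excess without PCI (8.5 points) already lies beyond the 7.5-point margin. The informative figure is the power under equal rates.

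What the reply does not remove is that the same section names both arms as the reference, and that the stated purpose, deciding "whether the extra procedure of pre-TAVI PCI can be safely avoided", has no planned bound behind it. The planned Kaplan-Meier curves and hazard ratio would show the direction of the result, but they set no criterion for omission.

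**Conclusion.** The contradiction is real and should be settled before analysis. The planned test answers whether adding PCI is worse by 7.5 points or more. It does not answer whether PCI can be omitted. At the planning rates a positive result requires an observed difference of about -1.7 points or lower, and leaves the upper limit for the excess risk of omission at about 10.9 points or more. Success therefore cannot support avoiding PCI. Failure would not support it either, since failing to rule out harm from PCI does not bound the harm of omitting it.

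The figures rest on 1:1 allocation, independent components and a binary approximation. The agreement with the stated 88.8% makes these plausible. The additive composite leads to the same conclusion, which would change only if event rates fell below about 19%.

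**What to change.** - Keep the powered test (PCI minus no PCI, upper one-sided 95% limit below 7.5 points) as primary.
- In the second paragraph of Hypothesis, design and end points, correct the description of PCI as the active control and the statement about safely avoiding it, so that the reference arm is the same throughout.
- State that success means only that adding PCI is not worse by 7.5 points.
- Prespecify the two-sided 90% confidence interval for PCI minus no PCI, read against +7.5 (primary) and -7.5 (secondary, bearing on whether PCI can be omitted). State that power for the secondary bound at N = 310 is only about 36-40% even if the true rates are equal (assumed 32-45%).

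This costs wording and a second bound read from the same interval. It needs no extra patients or data.

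If the sponsor prefers to make omission of PCI the primary question, that is a different trial. Direction, margin and power must all be re-derived. The 7.5-point margin could not simply be carried over, because it equals 88% (7.5/8.5) of the benefit that the planning rates attribute to PCI. With that margin, 310 patients would not give the stated 88.8% power. Even with equal true rates, 80% power would need roughly 1,000 to 1,150 patients.

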### Patient population

Patient eligibility will be confirmed by the study investigators according to the inclusion and exclusion criteria in Table 1.

**Table 1 Tab1:** **Eligibility criteria for the percutaneous coronary intervention prior to transcatheter aortic valve implantation (ACTIVATION) trial**

Inclusion criteria	
	Definition
• Patients ≥18 years of age	
• Severe aortic stenosis, as defined by	• Peak transvalvular gradient of ≥40 mmHg on transthoracic echocardiography (TTE), transesophageal echocardiography (TOE) or dobutamine stress echocardiography (DSE)
	• Aortic valve area of <1.0 cm^2^
• Symptoms suggestive of aortic stenosis	Dyspnea, syncope *etc.* but not pre-dominantly angina
• Deemed of prohibitive risk for open aortic valve replacement by a TAVI multidisciplinary team (MDT) and accepted for TAVI by said TAVI MDT.	
Significant coronary artery disease	• ≥1 stenosis of ≥70% in a major epicardial artery deemed suitable for PCI (≥50% if protected left main stem or vein graft)
• Undergoing TAVI via any accepted approach	Transfemoral, transapical, subclavian or transaortic
• Written informed consent	
**Exclusion Criteria**	Definition
• Recent acute coronary syndrome	Within 30 days of randomization
• Unprotected left main stem disease	
• Significant angina	CCS class ≥3
• Pregnancy	
• Active internal bleeding (except menstruation)	
• Allergy to heparin or GPIIb/IIIa inhibitors	
• Thrombocytopenia cells/mm^3^)	Platelet count <100,000
• Patients who have previously been enrolled in this study	
• Patients who are currently enrolled in any other study where involvement in ACTIVATION would involve deviation from either protocol	

TAVI, transcatheter aortic valve implantation; CCS, Canadian Cardiac Society; GpIIb/IIIa, glycoprotein IIb/IIIa.

### Primary endpoint

The primary endpoint is a composite of mortality and rehospitalization at 12 months since randomization. Mortality is defined as death due to any cause, the exact nature and date of which will be recorded. All deaths will be considered cardiovascular-related unless there is documentation to the contrary.

